## Abstract

**Background:**

Electroencephalography (EEG) studies indicate possible associations between tinnitus and changes in the neural activity. However, inconsistent results require further investigation to better understand such heterogeneity and inform the interpretation of previous findings.

**Objective:**

This study aims to investigate the feasibility of EEG measurements as an objective indicator for the identification of tinnitus-associated neural activities.

**Methods:**

To reduce heterogeneity, participants served as their own control using residual inhibition (RI) to modulate the tinnitus perception in a within-subject EEG study design with a tinnitus group. In addition, comparison with a nontinnitus control group allowed for a between-subjects comparison. We will apply RI stimulation to generate tinnitus and nontinnitus conditions in the same subject. Furthermore, high-frequency audiometry (up to 13 kHz) and tinnitometry will be performed.

**Results:**

This work was funded by the Infrastructure Grant of the University of Bern, Bern, Switzerland and Bernafon AG, Bern, Switzerland. Enrollment for the study described in this protocol commenced in February 2018. Data analysis is currently under way and the first results are expected to be submitted for publication in 2019.

**Conclusions:**

This study design helps in comparing the neural activity between conditions in the same individual, thereby addressing a notable limitation of previous EEG tinnitus studies. In addition, the high-frequency assessment will help to analyze and classify tinnitus symptoms beyond the conventional clinical standard.

**International Registered Report Identifier (IRRID):**

RR1-10.2196/12270

## Introduction

### Background

About 10%-15% of the general population is suffering from chronic subjective tinnitus, that is, consciously perceiving sound without the presence of physical sound sources [1]. Tinnitus can lead to health problems, distress, and psychological complaints and can substantially impair the quality of life [2]. In most cases, tinnitus occurs after cochlear damage such as sensorineural hearing loss [3], presbycusis [4], excessive noise exposure, and noise trauma [5]. Chronic tinnitus is also experienced by people with otherwise normal hearing [6]. Furthermore, tinnitus can be generated by head and neck injury, infections and neck illness, drugs, and other medical conditions [5] and may also be influenced by emotional and mental conditions [7]. Extensive causes and symptoms could complicate the diagnosis and treatment of tinnitus; to improve this, studies have proposed classifying tinnitus into different subtypes according to symptoms such as perceptual characteristics, laterality, loudness, or symptom severity, as well as the presence of tinnitus-associated disorders [8-10]. Alternatively, the categorization of tinnitus has been based on the response to applied treatments [11]. Nevertheless, an incomplete understanding of the underlying pathophysiology and the presence of numerous psychosocial and environmental factors that could influence intervention results may cause heterogeneity and preclude tinnitus subgrouping. As an effect, to date, there are no singularly effective clinical evaluation and treatment methods for subjective tinnitus [12]. Moreover, the current tinnitus diagnosis heavily relies on patient-reported assessments such as questionnaires. Currently, more objective assessment methods, which could provide physiology-based measures of comparison, do not exist.

As tinnitus often originates from peripheral and central auditory mechanisms [13,14], the assessment of abnormal neural activity may be a potential approach for objective diagnosis. A number of research groups have suggested that tinnitus is accompanied by changes in the brain [15-20] and can be examined using electroencephalography/magnetoencephalography (EEG/MEG) [17,19,21-27]. In particular, spontaneous brain oscillations, that is, the ongoing brain activity in the absence of external events, have been intensively investigated using EEG/MEG. Traditional EEG/MEG power bands of resting-state activity have been quantified between people with tinnitus and controls [17,22]. One theory explaining group differences in the EEG/MEG power within specific frequency bands focuses on the thalamocortical dysrhythmia model. This model predicts an increase of power in low frequencies (delta and theta bands) and high frequencies (gamma band) in the auditory cortex in subjects with tinnitus [18]. Furthermore, marked alterations of EEG/MEG oscillations across other brain regions and power bands have been reported in the prefrontal cortex [28-31], cingulate cortex [29-38], parahippocampus [15,26,31,34,36,37,39-42], and insula [26,37,43], implying the involvement of other brain areas and power bands. Nevertheless, poor matching of gender, age, and hearing loss status across groups, as well as other confounding factors, hinder the interpretation of study findings and generate inconsistencies [44]. To minimize variance across subjects, a within-subject measurement comparing the brain activity during a baseline period (tinnitus with abnormal brain activity) with a period after the suppression of tinnitus (stabilization of abnormal activity) may overcome this limitation.

Residual inhibition (RI) is a temporary forward tinnitus suppression mechanism, which can reduce or alleviate tinnitus loudness for a short duration after the presentation of an acoustic stimulus [45,46]. Previous work has compared the brain activity between baseline (tinnitus) and poststimulus (reduced tinnitus or nontinnitus) periods on the group level, observing reduced power in the delta frequency band in the temporal region after stimulus exposure, which is in accordance with the thalamocortical dysrhythmia [47]. In a different study, neural activity changes between pre- and poststimulus periods were detected in nonauditory cortices, that is, in the left anterior superior temporal gyrus, the motor cortex, and the posteromedial cortex by a single subject with musical hallucination using music as suppression stimulus [48]. Adjamian et al compared the neural activity during masking and resting state [24]. Sedley et al detected changes in the tinnitus-related neural activity on a single-subject level, indicating the potential for within-subject comparisons to minimize data heterogeneity [49]. Moreover, RI has been investigated with high-precision recordings of the neural activity by using intracranial monitoring of a single subject, in which tinnitus-linked, low-frequency neural oscillations were observed in auditory cortical regions, as well as other brain areas, and interacted with the middle- and high-frequency activity [50]. Reportedly, the distinct response of the neural activity to control stimuli that do not induce RI indicated that these changes correlated with RI [47,49]. Nevertheless, no comparison was performed with nontinnitus subjects perceiving RI stimuli, which could further demonstrate the correlation between RI and the tinnitus-associated neural activity.

This study aims to examine the brain activity in tinnitus and nontinnitus subjects using whole-scalp EEG recordings. RI will be used to modulate the tinnitus perception and enable a within-subject comparison. In addition, the RI stimuli will be matched with the tinnitus frequency of each participant, while the same low-frequency (0.5 kHz) control stimuli will be presented to all participants to exclude any effects of nonspecific sound-induced responses. We extend the applicable frequency range up to 13 kHz to enable a more accurate frequency identification of tinnitus and RI characteristics across a wider portion of the audibility range. Moreover, including nontinnitus subjects enables to compare between matched tinnitus and nontinnitus groups (ie, hearing loss characteristics) to determine whether the observed differences in the neuronal activity after RI are tinnitus-specific.

### Objectives

The primary objective of this study is to identify tinnitus-associated neural oscillations in resting-state (spontaneous) scalp EEG data. We hypothesize that differences due to RI in the power spectral density (PSD) of baseline (tinnitus) and poststimulus (reduced tinnitus) measurements within the same subjects can be detected in traditional EEG power bands. The secondary objectives of this project are as follows; (1) to improve understanding of the RI effect on the tinnitus-associated neural activity; (2) to identify differences in the PSD of the baseline period between the tinnitus and control groups; (3) to identify differences in the PSD of the poststimulus period between the tinnitus and control groups; and (4) to evaluate whether within-subject EEG data collection can reduce heterogeneity.

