#### Sample Size

To estimate the appropriate sample size, we used data from a previous study showing statistically significant differences between the PSDs of EEG recordings from tinnitus and nontinnitus participants [53]. The averaged power in the theta band was approximately 15.6 and 14.3 µV^2^ for the tinnitus and nontinnitus subjects, respectively, and the pooled SD was 0.5 µV^2^. A power analysis to test a two-sided hypothesis at a significance level of.05 and a power of 80% was estimated to require a sample size of 39 participants in each group. Up to 50 participants in each group meeting the eligibility criteria after pre-enrollment and the screening session will be recruited.

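### Secondary objective 3 compares poststimulus levels and no listed objective compares the groups' change after residual inhibition, so the stated between-group contrasts cannot by themselves show tinnitus-specificity

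*Protocol article*

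**What the plan says.** All places are in the protocol article.

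- **Purpose of the controls (Introduction, Background).** Matched nontinnitus subjects are included "to determine whether the observed differences in the neuronal activity after RI are tinnitus-specific". The same paragraph relies on a 0.5 kHz control stimulus to rule out nonspecific responses to sound.
- **Primary hypothesis (Objectives).** It is a change within persons: "differences due to RI in the power spectral density (PSD) of baseline (tinnitus) and poststimulus (reduced tinnitus) measurements within the same subjects can be detected".
- **Secondary objective 2 (Objectives).** "to identify differences in the PSD of the baseline period between the tinnitus and control groups".
- **Secondary objective 3 (Objectives).** "to identify differences in the PSD of the poststimulus period between the tinnitus and control groups".
- **Expected baseline gap.** The Background cites a model that predicts raised delta, theta and gamma power in tinnitus. The Sample Size section takes a group difference from a previous study: "The averaged power in the theta band was approximately 15.6 and 14.3" µV² for tinnitus and nontinnitus subjects, with a pooled SD of 0.5 µV².
- **Expected effect of suppression (Background).** The argument for a within-subject design compares the tinnitus baseline "with a period after the suppression of tinnitus (stabilization of abnormal activity) may overcome this limitation".
- **Model (Statistical Analysis).** A linear mixed model has group, time-point and stimulus type as fixed effects and subject as a random effect.

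**The concern.** Whether the shift after RI is tinnitus-specific is a question about change: does power move more from baseline to poststimulus in tinnitus subjects than in controls? The objectives split this into two level comparisons, one at baseline and one at poststimulus, and neither is a difference in change. Finding one of them significant and the other not does not test whether the gap changed.

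The level comparison is also awkward on the plan's own premises. If the groups differ at baseline and suppression moves abnormal activity towards normal, RI shrinks the poststimulus difference. If RI does nothing, the baseline gap carries over intact. A significant objective 3 could then be reported as a poststimulus finding when it is only the earlier gap. A null result could mean normalization or low power. What is at stake is the inference for which the control group was recruited.

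**Working it through.** **1. The plan's own figure.** For two means, n per group = 2(1.96 + 0.842)² × (SD/difference)². With difference 15.6 − 14.3 = 1.3 and SD 0.5, this is 2 × 7.85 × 0.148 = 2.3, so 3 per group (4 with the t distribution). The stated 39 is not reproduced. It needs an SD of about 2.05 (normal) or 2.02 (t), a standardized difference of about 0.64, whereas 1.3/0.5 = 2.6. That mismatch is a separate matter. Here it means that both SDs must be shown.

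**2. Set-up.** Baseline gap 1.3 and n = 39 per group. Two quantities are assumed because the article does not give them: f, the share of the gap that RI removes, and r, the within-person correlation between baseline and poststimulus power. Controls are assumed not to change.

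- Level contrast (objective 3): true value 1.3(1 − f), SE = SD × √(2/39) = 0.2265 × SD.
- Change contrast (group by time): true value 1.3f, SE = 0.2265 × SD × √(2(1 − r)).
- Chance of significance, two-sided 5%: Φ(value/SE − 1.96) + Φ(−value/SE − 1.96).

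**3. Worked entries.**
- Level, SD 2.05, f = 0: 1.3/0.464 = 2.80, giving 80%. At f = 0.5: 0.65/0.464 = 1.40, giving 29%.
- Level, SD 0.5, f = 0.5: 0.65/0.113 = 5.74, giving nearly 100%.
- Change, SD 2.04, r = 0.8, f = 0.5: SD of change = 2.04 × √0.4 = 1.29 and SE = 0.292, so 0.65/0.292 = 2.22, giving 60%.

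**4. Chance of a significant result.**

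| Contrast | f = 0 | f = 0.5 | f = 1 |
|---|---|---|---|
| Level, SD 2.05 (implied by 39) | 80% | 29% | 5% |
| Level, SD 0.5 (as stated) | 100% | 100% | 5% |
| Change, SD 2.04, r = 0.5 | 5% | 29% | 80% |
| Change, SD 2.04, r = 0.8 | 5% | 60% | 99% |
| Change, SD 0.5, r = 0.5 | 5% | 100% | 100% |

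At the stated SD, the level test still gives 82% at f = 0.75 and falls to 21% only at f = 0.9. A noncentral t calculation with standardized gap 0.642 gives the same 80%, 29% and 5% for the first row.

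**5. The case without a baseline gap.** If the groups do not differ at baseline and RI shifts only the tinnitus group by 1.3, the level test has about 80% power at SD 2.04. It then does respond to RI, so the reversed pattern depends on a gap being present.

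**The case against.** **Objective 3 is a legitimate question in itself.** Whether power in the suppressed state still differs from controls is worth asking, and the Objectives do not say that objective 3 is the test of tinnitus-specificity. This stands. It is a reason to keep the comparison, not to let it carry the inference: no other listed objective states the contrast that the Background calls for, and secondary objective 1, on understanding the RI effect, is too general to supply it.

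**The model may contain the needed contrasts.** Group, time-point and stimulus type are all in the mixed model, and interactions are commonly left to an analysis plan, which is not shown here. This also stands. A reader might infer that the trial cannot answer the specificity question. The documents do not support that, since the data and model factors are there. What is fixed badly is the wording of the between-group objectives.

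**The reversed pattern is conditional.** A reader might infer that objective 3 will simply be significant when RI fails and null when it works. That needs a real baseline gap, unchanged controls and near-complete normalization. The Background calls earlier group findings inconsistent, and eligibility requires only a 2-point loudness reduction, so partial suppression qualifies. At the stated SD, a halved gap is still nearly always significant.

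**The change contrast is not always more powerful.** At r = 0.5 and a halved gap, both tests give 29%. Its advantage in power depends on a correlation that the article does not give. The case for it is that it estimates the right quantity.

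**Conclusion.** The point holds as a defect in the stated objective. A single time-point comparison of non-randomized groups mixes a pre-existing difference with any RI effect, and that needs no numerical assumption. As worded, secondary objective 3 cannot alone show that the change after RI is tinnitus-specific.

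The size depends on assumptions. Given a baseline gap of 1.3 and no change in controls, the level test is most likely to be significant when RI does nothing. It falls to 5% only as RI approaches full normalization. With the SD implied by 39 per group it runs 80%, 29%, 5% as RI removes none, half or all of the gap. With the stated SD of 0.5 it cannot distinguish halving the gap from no effect, being near 100% in both. The change contrast starts at 5% when RI does nothing and rises with the RI effect at every SD and correlation examined.

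The primary within-subject comparison and the data collection are unaffected.

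**What to change.** State as the between-group objective the group difference in baseline-to-poststimulus change in power after the RI stimulus (group by time), together with the contrast of that difference with the corresponding one after the 0.5 kHz control stimulus (group by time by stimulus type). Report both with 95% confidence intervals from the planned mixed model. The second contrast is needed because the groups could differ in their general response to sound, which is what the control stimulus is there to exclude.

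Keep the poststimulus level comparison as a supportive analysis, and say that it is not evidence of tinnitus-specificity.

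The cost is one sentence in the Objectives and the added contrasts, with no new data. The three-way contrast will usually be less precise: if the two changes had equal SD and were uncorrelated within a person, its standard error would be √2 ≈ 1.41 times that of the two-way contrast.

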## Methods

### Study Design

#### Background

This research project is an observational study with a mixed design and will be conducted at the Department of Otolaryngology, Head and Neck Surgery at the Bern University Hospital, Inselspital, Bern, Switzerland. The protocol was designed in accordance with the ethical principles in the Declaration of Helsinki and has been approved by the local institutional review board (reference number: 2017-02037).

#### Participants and Eligibility Criteria

To participate in this study, tinnitus participants have to fulfill the following inclusion criteria: (1) age ≥18 years; (2) subjective tinnitus, that is nonfluctuating; (3) a single-pitched tinnitus perception that is unilateral, bilateral (in both ears), or central (in the head); (4) a difference between the loudness discomfort level (LDL) and minimum masking level (MML) of at least 20 dB; (5) “mild” to “severe” tinnitus, that is, a Tinnitus Handicap Inventory score between 18 and 76 [51]; and (6) sensitivity to RI, that is, a reduction of at least 2 points on a Likert scale of tinnitus loudness change (−5 to +5) directly after the presentation of the acoustic stimulus and for that reduction to be repeated at least 7-10 presentations (see section “Residual Inhibition”).

The exclusion criteria for tinnitus subjects are as follows: (1) LDLs preventing RI stimulation (see section “Tinnitometry”); (2) a history of central nervous system, cardiac, neurologic, psychiatric, or other major diseases or drug abuse, deemed clinically significant at the time of the study by the investigator (Multimedia Appendix 1 for details); (3) moderate or severe depression or generalized anxiety indicated by a Hospital Anxiety and Depression Scale score of at least 11 points on either subscale [52]; and (4) any participant who experiences RI after the 0.5 kHz control stimulus.

Non-tinnitus controls need to meet the following criteria for the study inclusion: (1) age≥18 years; (2) no tinnitus defined by self-reporting; and (3) comparable audiogram to one of the tinnitus subjects, that is, within ±15 dB at each of the frequencies of the extended air conduction hearing thresholds. The values can exceed this threshold at a maximum of 2 frequencies but not at the tinnitus pitch and control frequency.

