### Study Procedure

Table 1 provides an overview of the study procedure. During pre-enrollment, a checklist will be filled by potential study participants to assess the tinnitus-associated psychological status (tinnitus subjects only), general health conditions, neurological conditions, and medical history. Potential study participants will then be invited to the screening session to assess the study eligibility. The total duration of the screening session will be 70 minutes for tinnitus subjects and 35 minutes for nontinnitus subjects. Eligible subjects will be invited to the assessment session with a total duration of 150 minutes, including preparation and postassessment cleaning time. The assessment consists of 2 subsessions with 30 minutes each, separated by a 10-minute break. All participants will be asked to avoid the consumption of coffee 5 hours before the assessment session [54].

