#### Medical History and Questionnaires

The medical history contains information about the patients’ health status and the cause of their tinnitus such as the presence of cardiovascular diseases, tinnitus objectivity, signs of otorrhea, and other external or middle ear diseases and drugs that can directly influence the analysis. The following questionnaires will be administered to assess the effects of tinnitus, co- occurring complaints, and health-related quality of life: (1) a general health checklist, aimed at identifying health problems that could affect the brain activity of interest; (2) the Tinnitus Handicap Inventory [56] to assess the severity of tinnitus symptoms; and (3) Hospital Anxiety and Depression Scale [52] to assess depression and anxiety.

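### The health, drug-abuse and depression/anxiety exclusions are written for tinnitus subjects only, which leaves the between-group PSD comparisons open to confounding

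*Protocol article*

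**What the plan says.** The section Participants and Eligibility Criteria treats the two groups separately. Its single exclusion list opens "The exclusion criteria for tinnitus subjects are as follows". Two of its four items are not specific to tinnitus or to residual inhibition:

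- Item (2) covers "a history of central nervous system, cardiac, neurologic, psychiatric, or other major diseases or drug abuse, deemed clinically significant at the time of the study", as judged by the investigator, with details in Multimedia Appendix 1.
- Item (3) covers "moderate or severe depression or generalized anxiety indicated by a Hospital Anxiety and Depression Scale score of at least 11 points on either subscale".

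The control criteria are introduced by "Non-tinnitus controls need to meet the following criteria for the study inclusion" and number three: adult age, no self-reported tinnitus, and an audiogram comparable to that of one tinnitus subject. No exclusion list for controls follows.

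Two other sections bear on this. Under Study Procedure, potential participants fill in a pre-enrollment checklist "to assess the tinnitus-associated psychological status (tinnitus subjects only), general health conditions, neurological conditions, and medical history". Under Medical History and Questionnaires, the instruments include "a general health checklist, aimed at identifying health problems that could affect the brain activity of interest", and HADS is listed without saying which group completes it.

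**The concern.** Secondary objectives 2 and 3 compare PSD between the tinnitus and control groups at baseline and after the stimulus. The Introduction relies on matched groups to judge whether differences are specific to tinnitus, and it faults earlier work for poor matching and other confounders. The matching described here covers hearing only.

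If one group is cleared of major disease, drug abuse and marked depression or anxiety and the other is not, a PSD difference may partly reflect that difference in health. The stated purpose of the health checklist shows that the authors themselves regard such conditions as relevant to the brain activity under study. The tinnitus versus nontinnitus contrast also underlies the sample size, so it is not peripheral.

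**Working it through.** **1. The two groups side by side, as written**

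| Condition | Tinnitus subjects | Controls |
|---|---|---|
| Major neurological, cardiac, psychiatric or other disease; drug abuse | Excluded, item (2) | No rule stated |
| HADS of at least 11 on either subscale | Excluded, item (3) | No rule stated |
| General health, neurological conditions, medical history collected before enrollment | Yes | Yes |
| HADS collected | Yes | Unclear |

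The last row is unclear because Study Procedure limits the tinnitus-associated psychological part to tinnitus subjects. That could mean the Tinnitus Handicap Inventory alone or HADS as well.

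**2. Which comparisons are exposed**

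- Primary objective: baseline against poststimulus within the same subjects. Controls do not enter it, so it is unaffected.
- Secondary objectives 2 and 3: PSD levels compared between groups. A stable difference in health mix does not cancel here.

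**3. Size of a possible shift**

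The documents give no figure for this, so the inputs are assumptions:

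- p = share of controls who would fail item (2) or (3): 5-20%. The share in the tinnitus group is taken as 0, because the exclusions are applied there.
- D = average difference in band power between those controls and the others, in between-subject SDs: 0.5-1.0, sign unknown.

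Shift in the control mean = (1 − p) × 0 + p × D = p × D.

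- Low corner: 0.05 × 0.5 = 0.025 SD.
- High corner: 0.20 × 1.0 = 0.20 SD.

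**4. Set against the planning effect**

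The Sample Size section gives means of 15.6 and 14.3 µV² (difference 1.3), SD 0.5, two-sided 5% level, 80% power and 39 per group. These inputs do not reproduce 39: 2 × (1.96 + 0.84)² × 0.5² / 1.3² ≈ 2.3, so 3 per group, or 4 by t-test. That is a separate matter, but it leaves two possible yardsticks:

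- Printed inputs: d = 1.3/0.5 = 2.6. The shift is 0.025/2.6 = 1% to 0.20/2.6 = 8% of the planning effect.
- Effect that 39 per group can detect by t-test: d ≈ 0.64, implying an SD of 1.3/0.64 ≈ 2.02 µV². The shift is 0.025/0.64 = 4% to 0.20/0.64 = 31%.

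**The case against.** The strongest reply is that controls are in fact screened. They complete the checklist, and the Sample Size section speaks of recruiting people in each group who meet eligibility after pre-enrollment and screening. Pre-enrollment consists only of medical history and questionnaires (Table 1), which suggests that those answers inform eligibility in both groups. The list of excluded diseases is in Multimedia Appendix 1, which is not shown, and its title is not limited to tinnitus subjects. The article also condenses a fuller protocol.

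Part of this stands: practice may be more even-handed than the text, and the fuller protocol may say so. It does not remove the point. The article gives complete, separate criteria for each group and restricts the exclusions by name, so this is a stated rule and not an omitted detail. No section attaches a consequence to a control's checklist answers, and the eligibility text cites the appendix only inside the tinnitus list.

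Four stronger readings are tempting but not supported:

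- That the comparison is biased by design. The text establishes asymmetric selection. Whether bias results depends on who enrols.
- That nothing in the analysis could deal with it. The listed fixed effects are group, time-point and stimulus type, with no health or HADS term, but the analysis plan is not shown and covariates are commonly set there. Additive differences that are constant over time would also cancel from a group-by-time contrast, if one is fitted.
- That about 30% of the effect is at risk. That is the worst corner of two assumed ranges against a back-calculated effect.
- That controls have no HADS score. The documents leave this open.

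**Conclusion.** The point holds as a risk to the secondary between-group comparisons. Followed as written, the protocol admits a control with a condition that would exclude a tinnitus subject, including conditions the authors consider relevant to brain activity. Objectives 2 and 3 are open to confounding of unknown size and direction, about 0.03-0.20 SD if 5-20% of controls are affected and differ by 0.5-1.0 SD. Both ranges are assumptions. The change is worth making because it is cheap, not because a large bias has been shown.

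**What to change.** State in the eligibility section that exclusion items (2) and (3) also apply to controls, assessed from the checklist they already complete and from HADS given at pre-enrollment. If the exclusions already apply in practice, say so, and say how checklist findings in controls are acted on.

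For controls already enrolled, identify those who would fail from the checklist and from any HADS score recorded at pre-enrollment, and report objectives 2 and 3 with and without them. Do not use a HADS obtained later, because it would not describe the participant's state at the EEG recording.

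Cost: a short amendment and, if controls do not yet complete it, one more web questionnaire. A few controls may need replacing, each with a fresh audiogram match. Enrollment began in February 2018 and the article reports analysis as under way, so for much of the sample only the with-and-without report may be feasible. If controls have no HADS score, item (3) can be applied only to new controls, and the report should say so.
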